**Fig. 2 Fig2:**
[figure not shown]
Summarized steps of the NAT counselling intervention programme

## Objectives

The objectives of this study are (1) to test the sustainability of the ‘NAT counselling intervention’ within the German health system and to identify characteristics that hinder or facilitate its scalability in terms of acceptability, adaptation, implementation and effectiveness [126], (2) to estimate the cost-effectiveness of the programme, and (3) to assess the effectiveness of the preventive and protective peer-lead intervention NAT Narrative Trauma Work [125] on participants’ mental health, integration and overall well-being.

## Trial design

The present study employs a naturalistic parallel groups design, integrating a regression discontinuity statistical approach for quasi-randomisation with a classical longitudinal design. The resulting pattern of evidence will indicate the sustainability, cost-effectiveness and effectiveness of the programme while we ensure that all study participants receive evidence-based treatment.

Assessments include an in-person baseline screening, monthly online or assisted self-assessments (hereafter: well-being monitor), and an in-person follow-up at 6–9 months post-baseline. Given the central role of the peer counsellors in the programme, we will assess their training and supervision in terms of acceptability, efficiency and motivations, through focus group discussions and survey-based evaluations. These evaluations will take place before the counsellors begin their active work and after they have completed a substantial number of NAT steps (screenings, referrals, checklist intakes, lifeline sessions and narrative event-telling sessions).

## Methods: participants, interventions and outcomes

### Study setting

The programme will be implemented in two medium-sized cities and surrounding areas of Baden-Württemberg, Germany, in collaboration with two local NGOs. The NAT counselling intervention will take place within the initial intake facility, where asylum seekers are waiting to be assigned to their long-term accommodation by the responsible district authorities. Invitation and initial information about the programme will be provided by social workers, visits and information sessions by the NAT counsellor in the accommodation, and flyers handed out to refugees.

### Eligibility criteria

*Refugees.* All adult asylum seekers (≥18 years) living in or arriving at the collaborating initial intake facilities are eligible to participate in the study and are offered NAT step 1, the screening interview with RHS-15 including feedback and referral if needed. Exclusion criteria include: severe cognitive impairment or communication problems that prevent participation in interviews, as well as individuals with severe intellectual or psychiatric disabilities who would qualify for guardianship (legal/ethical considerations).

For NAT steps 2 (checklist intake), 3 (lifeline laying) and 4 (narrative event-telling sessions), participants with an RHS score (items 1–13) between 13 and 36 points (‘yellow group’) are eligible; exclusion and referral to specialist care will occur in the case of acute psychiatric illness, acute suicidal ideation or danger to others, as well as acute and persistent intoxication that would prevent effective NAT sessions.

All steps of the NAT counselling intervention are carried out by trained counsellors under the supervision of NET experts (from vivo international e.V. and the University of Konstanz) or otherwise trained licensed psychotherapists. The NAT counsellors themselves are peers in terms of their cultural and migrant background and therefore have similar biographical experiences, moreover are familiar with and well-integrated into German culture and have good language skills (mother tongue and German) and strong social skills. It is recognised that conditions in the countries of origin vary and therefore the requirements for recruitment and inclusion of counsellors in the project programme have not been rigidly defined but are rather based on the real-world setting. However, high motivation, impartiality and strong integrative and social skills are prerequisites for participation in the NAT training programme. Exclusion criteria for counsellors include: suffering from a mental illness, holding extreme or radical religious or ideological views, have insufficient language skills or illiteracy in German. In addition, we provide a screening for PTSD symptoms in an initial session using the PTSD Checklist for DSM-5 [127, 128]. Following this assessment, participants are provided with an individualised information session on the potential psychological impact of the project and supported to make their own decision as to whether or not they are ready to train and work as a counsellor and to undergo counselling themselves. Due to the sensitive nature of this personal health information, no written records are made or kept.

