The overarching objective of this project is to pick up the key elements of this extensive knowledge gained from diverse countries of origin of refugees and integrate these into the German mental health system. To this end, we introduce a stepped-care trauma rehabilitation programme [121, 122] expanding the system with a peer counsellor component called *‘NAT counselling intervention’*, which integrates a screen-to-counsel approach for refugees residing in temporary accommodation in Germany (see Fig. 2). The specific goals of the ‘NAT counselling intervention’ are: (1) to invite asylum seekers to participate in a screening session conducted by a trained and assigned peer NAT counsellor with a similar cultural background, to assess potential psychological sequelae of traumatic events; the results of the screening are evaluated, and the client is categorized based on the logic of a traffic light system: red, yellow, or green and then referred to appropriate help, based on the severity of score identified by the 15-item Refugee Health Screener [123], a validated tool with excellent psychometric properties to screen for trauma related symptoms and probable diagnoses [124]; (2a) to deliver a specific counselling intervention called *‘NAT Narrative Trauma Work’* [125], adapted from NET and delivered by counsellors, for refugees with subclinical levels of symptoms (‘yellow’ group; RHS score of 13–36); and (2b) to facilitate the referral of refugees with a high likelihood of trauma related disorders (‘red’ group’; RHS score of ≥ 37) to a licensed psychotherapist^1^ for appropriate treatment, or (2c) to monitor and reevaluate cases with low symptoms; (3) follow-up; and (4) monitor psychological resources that enable individuals to participate in the community and society (‘well-being monitor’).

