**Severe stress (RHS ≥ 37 or acute danger to self or others)**
Individuals in this category likely meet the diagnostic criteria for a mental health disorder or present an immediate danger to themselves or others. In such cases, individuals are referred to a licensed psychotherapist for clinical assessment and guideline-based treatment. Referrals are made to various service providers, including psychosocial centres, collaborating private practitioners, licenced psycho-therapists, outpatient clinics and hospitals. In cases of immediate danger to self or others, referrals for inpatient treatment may be necessary and directed to specialised clinical services in the region (psychiatric hospitals, acute care units, or, when appropriate, law enforcement).

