### Criteria for discontinuing or modifying allocated interventions

In the event of danger to self or others, deterioration of trauma reactions or signs of other (comorbid) psychological symptoms, the client will be re-assigned to the red group and receive psychotherapeutic service or treatment at an acute care facility within the German health system. Thereafter, treatment delivery will follow the principles of the red group in full extent.

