### Implementation

To assign participants according to the RDD principles, we will use the RHS-15 (items 1–13) as eligibility criteria with two critical thresholds at 13 and 36 (see Fig. 4) as foreseen in the stepped-care model of the *NAT counselling intervention*. The RDD then assumes that the allocation to the conditions is nearly random within the determined bandwidth (RHS sum scores just above or below the cutoffs) and potential factors that would manipulate treatment effect vary randomly across participants in both groups. The *fuzzy* versus the *sharp* design version takes into account real-world implementation settings recognizing that participants with RHS scores in the yellow range need to be assigned to the red group, for instance, in cases of suicidal ideation or other negative psychological developments that requires treatment by clinical psychologist.

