	The number of participants with subclinical symptom levels at baseline who do not require treatment after 6–9 months is higher in participants who received NAT than in the control group.	The number of participants with subclinical symptom levels at baseline who do not require treatment after 6–9 months is equal in participants who receive the adapted NET compared to the control group.	2b
Is NAT **effective** (symptom reduction)?	Symptom reduction in participants with subclinical symptom levels is stronger in participants receiving NAT than in the control group (see Table 1).	Symptom reduction in participants with subclinical symptom levels is the same in participants receiving NAT compared to the control group (see Table 1).	3
[4] Is the programme generally cost-**effective**?	The financial costs of the NAT counselling intervention are lower than those of other interventions.	The financial cost of the NAT counselling intervention is equal to or higher than other interventions.	4

[2a+b] Chi-squared tests will be used to compare the frequency of participants with subclinical symptom levels requiring more/less intensive treatment during the programme. Logistic regression analysis will be considered to estimate the odds of refugees with or without NAT requiring more/less intensive treatment (Table 4).

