### Methods in analysis to handle protocol non-adherence and any statistical methods to handle missing data

All eligible participants with reliable data and complete measures ( < 10% missing) at baseline will be included in the analysis. Participants who move into their long-term accommodation will remain in the study and follow-up will be continued. During the data collection periods we will give special attention to prevent missing data. One of the advantages of GLMMs over ANOVA is that it maximises the number of observations by excluding missing values only, rather than removing complete cases with some or all missing values present. This approach helps to maintain statistical power and reduce bias. In cases where missing data cannot be avoided, we use imputation methods using the mice R package [194] if more than 10% of the values in the entire dataset are missing, but no more than 30% per participant per assessment instrument. This threshold ensures that imputation is used judiciously and only when the amount of missing data is large enough to potentially affect the results, but not so large as to compromise the validity of the imputation process. We will conduct sensitivity analyses to compare results with and without imputation to assess the robustness of our findings. In addition, we will thoroughly document the patterns and reasons for missing data to inform the interpretation of results and discuss any potential biases introduced by missing data.

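### The prevention tests 2a/2b compare by NAT received and do not limit the control group to clients eligible for NAT, so clients excluded for acute conditions can be counted against the control

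*Protocol article*

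**What the plan says.** The Eligibility criteria have two tiers. Exclusions from the study cover "severe cognitive impairment or communication problems that prevent participation in interviews" and disabilities at guardianship level. A second list applies only to NAT steps 2, 3 and 4, for clients with RHS 13–36: "exclusion and referral to specialist care will occur in the case of acute psychiatric illness, acute suicidal ideation or danger to others", plus intoxication that would prevent effective sessions. Under the heading on informed consent, all refugees are invited to the face-to-face follow-up whatever their distress, so clients on the second list can supply outcomes.

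The aims at the end of the background section describe NAT as being for "refugees with subclinical levels of symptoms" and tie this to a score of 13–36. Table 2 (Intervention description) adds one non-score route to the red group: "Severe stress (RHS ≥ 37 or acute danger to self or others". The Implementation section says that "participants with RHS scores in the yellow range need to be assigned to the red group" in some cases and names a fuzzy regression discontinuity design (RDD) to allow for it. After allocation, on deterioration or danger, "the client will be re-assigned to the red group and receive psychotherapeutic service or treatment at an acute care facility".

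In Table 4, hypothesis 2a compares subclinical clients who received NAT with the control group on needing specialised psychotherapy after 6–9 months; 2b is the mirror image, on needing no treatment. Neither row says who forms the control group. The methods text for 2a+b plans chi-squared tests and a possible logistic regression to "estimate the odds of refugees with or without NAT requiring more/less intensive treatment". The missing-data section opens its analysis set with "All eligible participants with reliable data and complete measures" and does not say whether eligibility means for the study or for NAT.

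**The concern.** Every NAT client has passed the second list of exclusions. Nothing requires the same of a client without NAT. A client with RHS 28 and acute suicidal ideation at screening is subclinical by score, does not receive NAT, and is referred to specialist care at once. In 2a that client is likely to count as a control client who needs specialised care. In 2b the same client counts against the control again.

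The rule that separates the groups is thus close to the outcome itself. A few such clients can produce an apparent preventive effect, and the tests of 2a/2b as described do nothing to remove it.

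**Working it through.** The protocol states no rate or sample size for 2a, so there is no figure to reproduce. The check asks what 2a would show if NAT had no effect and excluded yellow-score clients were counted as without NAT.

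**Inputs (all assumptions except the significance level)**
- a = share of RHS 13–36 clients excluded for an acute condition: 5% (range 3–10%).
- p = need for specialised care at 6–9 months among all other yellow clients, with or without NAT: 10% (range 10–20%).
- q = the same need among excluded clients: 60–100%.
- w = share of the non-excluded clients without NAT: 50% (1:1 split), with 30% as an alternative.
- n = yellow clients with an outcome: 180–300. The Sample size section implies 450–750 participants in all (30–50% of about 1,500).
- Two-sided 5% level, so 2.5% in NAT's favour when there is no effect. The 95% level is in the Fig. 3 legend.

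**Control rate** = [a·q + (1−a)·w·p] / [a + (1−a)·w]. The NAT rate is p.

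- q = 100%, w = 50%: (0.05 + 0.0475) / (0.05 + 0.475) = 0.0975 / 0.525 = 18.6%. Odds ratio (0.10/0.90) / (0.186/0.814) = 0.49.
- q = 60%, w = 50%: (0.03 + 0.0475) / 0.525 = 14.8%. Odds ratio 0.64.
- q = 100%, w = 30%: (0.05 + 0.0285) / (0.05 + 0.285) = 0.0785 / 0.335 = 23.4%.

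**Chance of a significant result for NAT** = Φ[(d − 1.96·SE₀) / SE₁], where d is the difference in rates, SE₀ the pooled and SE₁ the unpooled standard error. Example with n = 300, q = 100%, w = 50%: 142.5 NAT and 157.5 control clients, pooled rate 14.5%, d = 0.0857, SE₀ = 0.0407, SE₁ = 0.0399. This gives Φ(0.15) = 56%.

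| Case (a = 5%, p = 10%, w = 50%) | n = 180 | n = 300 |
|---|---|---|
| q = 60% | 16% | 24% |
| q = 100% | 37% | 56% |

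Over the full range (a 3–10%, p 10–20%, q 60–100%, w = 50%) the odds ratio runs from 0.87 to 0.31 and the chance from 6% to 96%. With w = 30%, a = 5%, p = 10% and q = 100% it is about 59% at n = 150 and 79% at n = 250.

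**After the fix.** With the same exclusion on both sides, both rates equal p: the odds ratio is 1.00 and the chance returns to 2.5%.

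**Upper cutoff (36/37).** A simulation with no NAT effect fitted separate lines within 10 points of 36.5, with 5–25% of yellow clients near the cutoff excluded. With every client kept on the side given by the baseline score and no psychotherapy effect, the bias was −0.10 to +0.11 RHS points. With excluded clients taken to be 4 points worse at follow-up, it was −0.1 to −1.2 points if they were dropped and −1.2 to −2.8 points if they were moved to the comparison line. If psychotherapy lowered the red group's score by 4 points, all variants moved against NAT, by +1.2 to +4.0 points.

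**The case against.** The strongest reply is that the intended yellow control is the waiting list. The section on comparators calls its members NAT clients awaiting treatment, and a client referred elsewhere is not awaiting NAT. Table 2 also sends acute danger to red at any score, so waiting and NAT clients may pass much the same filter. This stands in part: the protocol does not say that excluded clients remain on the waiting list. But Table 1 defines that comparator by score alone, 2a/2b are not tied to it, and the analysis text speaks of all refugees with or without NAT. Table 2 covers only acute danger; acute psychiatric illness and intoxication appear as conditions only at the gate to steps 2–4.

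Second, 2a concerns need at 6–9 months, and referral at baseline does not establish that need. This is fair, and is why q goes down to 60%. The methods text for 2a+b speaks of need during the programme, which is less protective.

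Third, analysis sets are often left to an analysis plan, adjustment for confounders is promised, and the Limitations section concedes weak comparability. However, Table 4 itself words the contrast by NAT received, and no acute-condition covariate is named.

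A reader might also infer that the RDD contrast at 36/37 is biased for NAT, or that the bias always favours NAT. The documents support neither. Lines are fitted by side of the cutoff, the fuzzy design is named for these very clients, and eligible most naturally means eligible for the study. The comparator awaits or receives psychotherapy, which can push that contrast against NAT.

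**Conclusion.** The concern holds for 2a/2b. The protocol excludes and refers some RHS 13–36 clients from NAT only, keeps them in follow-up, and words the prevention contrast so that they can be counted as controls. If they are, the tests favour NAT under no effect. With 5% excluded and a 10% base need, the control rate is about 15–19% (1:1 split) or 23% (30% of the rest without NAT, all excluded clients in need), against 10%. False findings for NAT are roughly 16–56% with the 1:1 split and 6–96% over the wider range, against 2.5%.

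The direction follows from the wording and from the excluded clients having the greater need. The size rests wholly on assumed rates, and the bias disappears if the control group is limited to clients eligible for NAT. At the upper cutoff the point is one of clarity only: the handling of these clients should be stated.

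**What to change.** - Record at screening whether each of the NAT-step exclusion conditions is present.
- In 2a/2b and in the awaiting-NAT comparison, include on both sides only RHS 13–36 clients who met none of these conditions at screening. Name the control group in Table 4, and report the excluded clients separately.
- In the RDD, state that every screened client stays on the side given by the baseline score, with exclusion treated as non-receipt of NAT. This agrees with the fuzzy design already named.
- In the mixed models, do not count excluded yellow-score clients as NAT controls. Keep the red and green comparators of Table 1; the models should not be restricted to RHS 13–36.
- Reconcile the Eligibility criteria, the Implementation section and the analysis-set sentence in the missing-data section on how these clients are classed.

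The cost is one screening flag, some wording, and a slightly smaller 2a/2b sample. Referral and care are unchanged.

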### Who will take informed consent?

Prior to the initial screening, NAT counsellors will explain the programme and study details to potential participants. Written informed consent to participate will be obtained for both the screening and follow-up interview (see Appendix). Those eligible to participate in NAT will be asked to provide additional informed consent for participation in the intervention. All participants, regardless of their eligibility for NAT, will also be invited to complete the Well-being Monitor self-assessment. Separate informed consent will be obtained before the assessment begins. Finally, all refugees, irrespective of their level of distress and trauma symptoms, will be invited to complete the face-to-face follow-up.

### Additional consent provisions for collection and use of participant data and biological specimens

Not applicable as no biological data specimen will be collected.

## Interventions

### Explanation for the choice of comparators

In this naturalistic study, the following potential comparators to NAT (treatment condition) evolve: (1) NAT clients awaiting treatment; (2) clients with clinically relevant symptoms who are either (2a) waiting for psychotherapy or (2b) receiving psychotherapy; (3) clients without symptoms waiting for follow-up; and (4) clients before vs. after NAT (individual trajectories of symptom development, Table 1).

**Table 1 Tab1:** Constellation of comparators

Treatment condition	Control condition	Limitation	Mitigation
[1] NAT	Awaiting NAT (RHS 13–36)	Reduced follow-up time points for those who wait for treatment; unknown N	-
[2] NAT	[2a] PT waiting [2b] PT receiving	Clients might still wait but may have started, or already finished PT; higher symptoms of the control group at baseline	Statistical control for the number of treatment sessions, use of the RDD
[3] NAT	Watchful waiting (RHS < 13)	Lower symptoms of the control group at baseline, low symptom levels generally	Evaluate number of clients who present with improving vs. deteriorating symptoms rather than
[4] After NAT	Before NAT	Within subject comparison; potential confounding factors	-

Note: RHS-15 = 15 item Refugee Health Screener with a sum score indicating symptom severity; PT = Psychotherapeutic sessions provided by a licensed Psychotherapist. Threshold to clinical relevance is suggested for ≥37. Watchful waiting is indicated for clients with ≤12 points

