## Statistical methods

### Statistical methods for primary and secondary outcomes

#### Feasibility assessment

[1a-d] Descriptive statistics (frequencies, percentages, means, standard deviations) will be used to assess the feasibility of NAT and the NAT counselling intervention programme in general (Table 4). These quantitative measures will be complemented by qualitative data from focus groups conducted with NAT counsellors as participants. The focus groups will explore perspectives on the need for the programme, areas for improvement, perceived effectiveness, barriers and facilitators to implementation, participants’ experiences and suggestions for improvement (Table 4). Content thematic analysis will be used to analyse the qualitative data to provide a comprehensive understanding of the feasibility and potential for improvement of the programme, using Nvivo software for data analysis.

**Table 4 Tab4:** Summarises the research questions and associated specific hypotheses

Research question	Alternative hypothesis	Null hypothesis	Ref.
Is the overall programme **sustainable**?	The majority ( > 50%) of refugees who leave the temporary accommodation have taken part in the project.	The minority ( < 50%) of refugees who leave the temporary accommodation have taken part in the project.	1a
	The programme is evaluated positively by stakeholders (refugees, counsellors, social workers).	The programme is evaluated negatively by stakeholders (refugees, counsellors, social workers) regarding issues that cannot be improved.	1b
	Recommendation to indicated treatment is followed by more than 50% of refugees.	Recommendation to indicated treatment is not followed by more than 50% of refugees.	1c
	The majority ( > 50%) of trained counsellor perform the screening and provide the intervention.	Only a minority ( < 50%) of trained counsellors perform the screening and provide the intervention.	1d
Is NAT **effective** (prevention)?	The number of participants with subclinical symptom levels at baseline who require specialised psychotherapeutic treatment after 6–9 months is lower in participants who received NAT than in the control group.	The number of participants with subclinical symptom levels at baseline who require specialised psychotherapeutic treatment after 6–9 months is equal in participants who receive the adapted NET compared to the control group.	2a

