[3] To assess the effectiveness of NAT compared to the comparison groups (see Tables 1 and 4), we will combine the figures resulting from RDD with traditional approaches (GLM, clinical significance). In the RDD, we will calculate a local average treatment effect (LATE) of the intervention on primary (RHS-15) and secondary (LSNS, BRS, SWLS, SSS8) outcomes (see Table 1). To this end, we will firstly test whether the main criteria for a valid RDD are held. Using a graphical method (scatterplot), we will examine the relationship between the eligibility (RHS at baseline) and outcome (follow-up) variables. We expect the RHS score to be discontinuous at the cutoff values. In contrast, we do not expect to see discontinuities in relevant covariates at the cutoff, which would violate the assumptions of an RDD. Next, separate regression lines will be fit on both sides of a cutoff value using an ordinary least squares (OLS) regression as the starting point. Alternative functional forms will be tested with the goal of ensuring an unbiased estimation. The LATE will be computed directly as the difference between the regression lines at the cut-off (intercept). To test the statistical significance of the difference between the two conditions, we will use a *t*-statistic, dividing the treatment effect (difference between regression lines at cut-off) by the sum of the square of the standard errors of the comparison group (*SE*_*comparison*_) and the intervention group (*SE*_*interventio*n_). The calculated *t*-statistic will then be compared to a critical value from the *t*-distribution for the given degrees of freedom (*DF*). The degrees of freedom will be determined based on the number of the observations and the parameters estimated in the two separate regressions. In the most simple form, *DF = n*_*comparison*_
*+ n*_*intervention*_
*- 4*. The test will be two-sided. Moreover, we will run falsification tests and sensitivity analysis to ascertain the validity of the RDD [178], examine whether results are sensitive to the choice of bandwidth [144], run placebo tests on exogenous covariates and on the outcome at values other than the actual cutoffs [145]. Prespecified subgroup analyses will explore potential heterogeneity in treatment effects across different demographic and clinical characteristics. Adjusted analyses will account for potential confounding factors identified a priori.

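### The upper-cutoff comparator in Table 1 row [2] is defined by psychotherapy status after screening, and neither the RDD nor adjustment for session count removes that selection

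*Protocol article*

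**What the plan says.** Under 'Explanation for the choice of comparators', the article names as one comparator "clients with clinically relevant symptoms who are either (2a) waiting for psychotherapy or (2b) receiving psychotherapy". Row [2] of Table 1 lists these as control conditions [2a] and [2b]. Its limitation column reads "Clients might still wait but may have started, or already finished PT; higher symptoms of the control group at baseline", and its mitigation column reads "Statistical control for the number of treatment sessions, use of the RDD".

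Assignment rests on the baseline score alone. Under 'Implementation', "we will use the RHS-15 (items 1–13) as eligibility criteria with two critical thresholds at 13 and 36", and "The RDD then assumes that the allocation to the conditions is nearly random within the determined bandwidth". Scores of 13–36 (yellow) lead to NAT. At 37 or above (red), "individuals are referred to a licensed psychotherapist for clinical assessment and guideline-based treatment".

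Hypothesis 3 in Table 4 takes its control group from Table 1. Item [3] of the statistical methods does the same: "To assess the effectiveness of NAT compared to the comparison groups (see Tables 1 and 4), we will combine the figures resulting from RDD". Conventional models are to be used alongside. The effect is the difference between two regression lines at the cutoff, tested two-sided. The article does not say that [2a] and [2b] stay together on the red side, nor at what time a client counts as waiting or receiving.

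**The concern.** An RDD treats people just below and just above a cutoff as comparable because the score alone puts them on one side or the other. That argument covers everyone screened on each side. It does not cover a subset of one side picked out by something that happens afterwards.

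Therapy status is such a thing. Row [2] itself accepts that it moves between screening and follow-up. Clients who decline referral fit neither [2a] nor [2b]. The section on discontinuing or modifying interventions also moves deteriorating yellow clients into red-group care, so a group defined by receiving therapy could include people screened on the other side of the cutoff.

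The two listed mitigations do not close the gap. The RDD answers the higher baseline symptoms. Session count is a later consequence of the same process that produces therapy status. At stake is the reading of hypothesis 3: a jump against waiting or receiving clients alone could be taken as evidence about NAT when it partly reflects who started therapy, or what therapy did.

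**Working it through.** The article gives no numerical bias, effect or power for the upper cutoff in its text, so there is no figure to reproduce. The check is a simulation in which NAT truly does nothing.

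**From the article:** cutoff between 36 and 37; separate straight lines on each side; effect = difference of the lines at the cutoff; two-sided test; 5% level (from the 95% level in the power figure legend).

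**Assumed, not in the article:**
- 300 clients within 8 RHS points of the cutoff. Expected participation is 0.30 × 1,500 = 450 to 0.50 × 1,500 = 750 in all, and the number near the cutoff is not given, so 300 is generous. A smaller number would leave the average shift unchanged but bring false positives closer to 5%.
- Residual SD of 7 points, including an unmeasured prognostic factor U that is continuous at the cutoff and worth b = 4 points per SD (varied 2 to 6).
- Half of red clients start psychotherapy by follow-up (varied 20% to 80%).
- Log-odds of starting of −1 to +1 per SD of U. Positive means that clients with a worse prognosis start sooner.
- About 8 sessions on average among starters, none otherwise.
- t = jump / √(SE₁² + SE₂²), the conventional form, so that any excess false positives come from selection alone.

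**Formula.** With no treatment effect, jump against a subset = −b × E[U | subset], where jump is the NAT side minus the red side. A positive jump makes NAT look worse. Over all red clients E[U] = 0, so the expected jump is 0.

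**Results, NAT effect 0 and psychotherapy effect 0, half starting, b = 4.** Mean jump in RHS points (false-positive rate), 3,000 runs per row:

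| Log-odds of starting per SD of U | Waiting only [2a] | Receiving only [2b] | All referred | All referred, session-adjusted |
|---|---|---|---|---|
| 0 (capacity only) | −0.03 (4.9%) | −0.01 (5.2%) | −0.02 (5.3%) | −0.03 (4.9%) |
| +0.5 | +0.96 (8.2%) | −0.95 (7.6%) | +0.01 (4.9%) | +0.76 (7.4%) |
| +1.0 | +1.66 (13.6%) | −1.69 (14.6%) | −0.01 (4.8%) | +1.32 (12.0%) |
| −0.5 | −0.99 (9.6%) | +0.97 (7.9%) | −0.01 (5.7%) | −0.78 (9.1%) |
| −1.0 | −1.64 (13.1%) | +1.68 (14.3%) | +0.02 (4.6%) | −1.31 (12.0%) |

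Checks on the table: at +0.5 the waiting group is 0.96 / 4 = 0.24 SD better in prognosis, and at +1.0 it is 1.66 / 4 = 0.415 SD better. Weighting the halves recovers the pooled result: 0.5 × 0.96 + 0.5 × (−0.95) = 0.005.

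**Sensitivity at log-odds +0.5.** Varying b from 2 to 6 gives +0.55 to +1.36 against [2a] and −0.45 to −1.43 against [2b]. Varying the share starting from 20% to 80% gives +0.46 to +1.45 against [2a] and −1.55 to −0.46 against [2b].

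**If psychotherapy lowers RHS by 4 points, with start unrelated to prognosis:** −0.02 against [2a], +3.99 against [2b], +1.99 against all referred. The [2b] jump is then the whole psychotherapy effect. The pooled jump is 0.5 × 4 = 2, the correct contrast with referral when half receive therapy. Session adjustment leaves +0.38 where the true NAT effect is 0.

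**The case against.** The strongest reply is that the article plans no split RDD. It assigns by score, fits lines on each side of a cutoff without mentioning therapy status, includes all eligible participants with adequate baseline data, and invites everyone to follow-up. Rows [2a] and [2b] share one line of a table of potential comparators. On a natural reading, session adjustment answers the changing therapy status and the RDD answers baseline severity, and adjusting for sessions suggests a pooled red side. The Limitations section concedes that randomisation within the control groups is compromised, and pooling rules may sit in a fuller document.

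Much of this stands. A reader might infer that two separate RDDs, against waiting and against receiving clients, are promised; no section says so. A reader might also infer that almost half of red clients would fall outside both groups, from hypothesis 1c, "Recommendation to indicated treatment is followed by more than 50% of refugees". That threshold covers every indicated treatment, NAT included, and is no estimate of uptake among red clients.

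The objection does not remove the point. The article names the control conditions by therapy status and directs hypothesis 3 and the RDD to them. The general concession prescribes nothing. Even on the favourable reading, a pooled red side with session adjustment, the selection returns, as the last column of the table shows.

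**Conclusion.** The point holds in a conditional form. Table 1 defines the upper-cutoff comparator by a status that arises after assignment, and its stated mitigation addresses baseline severity but not that status.

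It would be tempting to conclude that the upper-cutoff jump is biased as planned, or biased in NAT's favour against waiting clients. The documents support neither. Bias arises only if therapy status is related to prognosis. The article makes that plausible: its background describes avoidance, scepticism and fear as barriers to care, and clients in immediate danger may be routed to inpatient treatment. It does not show it. A queue set purely by capacity gives no bias, and the sign reverses with the direction of selection.

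Where selection exists, the illustration gives about 1 to 1.7 RHS points in either direction and 8–15% false positives in place of 5%, at b = 4 with half starting therapy. These sizes rest on the assumed inputs and cannot be derived from the article. Separately, if psychotherapy works, the jump against [2b] reflects psychotherapy as well as NAT. Keeping all referred clients together, without session adjustment, gave a null jump of about 0 and 4–6% false positives in every setting with no treatment effect.

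**What to change.** In Table 1 row [2] and item [3] of the statistical methods:

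- Define the upper-cutoff RDD as all clients screened at RHS 37 or above, whatever became of the referral (waiting, receiving, finished or declined), against all clients screened on the yellow side, whether or not NAT was started.
- Do not adjust this contrast for number of sessions.
- State that it is the as-screened (reduced-form) jump on which any fuzzy-RDD estimate is built, and that it contrasts allocation to NAT with referral to psychotherapy as referral works in practice.
- Report psychotherapy status on the red side descriptively, with the time point at which it is classified.
- Label contrasts with [2a] or [2b] alone, and session-adjusted analyses, as exploratory, with no role in deciding hypothesis 3.

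The cost is wording. No new data are needed, because everyone is already invited to follow-up regardless of distress. The sponsor gives up separate RDD claims of NAT against waiting and NAT against receiving clients, which the score-based assignment does not identify.
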